### Retention

7.5

To make families feel part of the research team, a special family friendly retention concept will be in place. Participating families will benefit from special care and support; families will be reimbursed for travel expenses and children will receive small gifts during visits. The advantages of study participation will be clarified to parents, such as free monitoring of children's health status and the potential benefit of the intervention. Newsletters and reports on islet autoantibody tests as well as community building activities (homepage, Facebook groups) will also be used as a retention strategy. For further information refer to the GPPAD homepage: https://www.helmholtz-munich.de/en/idf/studies/avant1a-study.

## Safety reporting

8

The investigators are responsible for the recording and reporting of AEs observed from randomisation (for UK sites: from consent) until 1 month after administration of the study medication. All AEs should be followed until event resolution or stabilisation or participant completion of the trial, whatever occurs first. The causality assessment of an Adverse Event Following Immunisation (AEFI) are outlined in the Safety Management Plan.

## Statistics

9

All efficacy analyses will be performed on the modified intention-to-treat (mITT) population unless otherwise specified. The mITT population will include all randomised subjects who have received at least 1 dose of study drug. An analysis will also be performed on the per protocol population that will include all participants who complete the 3 vaccination visits. The overall difference between the groups in the cumulative incidence functions will be tested by the log-rank test at the two-sided significance level of 0.05. The hazard ratio of the two groups and its 95 % confidence interval will be determined by the Cox model. As a sensitivity analysis, the hazard ratio of the two groups will be assessed using the Cox regression when including site as covariate. The estimates of cumulative incidence and the log-rank test will adjust for periodic outcome assessment visits to assess islet autoantibody status. The secondary endpoints will be analysed using the same statistical methods as the primary endpoint.

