### Inclusion criteria

6.2

Each potential subject must satisfy all of the following criteria in order to permit enrolment in the study:1.Age between 3.00 and 4.00 months at the time of enrolment.2.A high genetic risk (>10 %) to develop islet autoantibodies by age 6 years:a)For children without a first-degree family history of type 1 diabetes, high genetic risk is defined as a DR3/DR4-DQ8, DR4-DQ8/DR4-DQ8 or DR4-DQ8/DR4-DQ7 and an rs6901541 C/T genotype and an elevated sex-specific genetic risk score that is at the 98.75th centile, in other words identifies around 1.25 % of newborns without a first-degree family history with type 1 diabetes.b)For children with a first-degree family history of type 1 diabetes, high genetic risk is defined as having HLA DR4 and DQ8, none of the following protective alleles: DRB1∗1501, DQB1∗0503, DRB1∗1303, and a sex-specific genetic risk score >50th centile of the background population. These represent around 25 % of children with a first-degree family history of type 1 diabetes.3.Written informed consent signed by the custodial parent(s).

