### Study power and accrual target

9.2

The sample size calculation was based on the numbers needed to test the hypothesis that COVID-19 vaccination will reduce the incidence rate of islet autoantibodies in children with a high genetic risk to develop type 1 diabetes. The trial numbers were determined for 70 % power to detect a 26 % reduction in islet autoantibodies in the treated group at a two-tailed significance of 0.05. The expected infection rate until age 2.5 years used to determine the trial numbers will be 60 %. The trial numbers were based on a 2-fold increase in the risk for islet autoantibodies in infected versus non-infected children. Therefore, the risk by age 4 years is expected to be 8.75 % in uninfected children and 17.5 % in infected children. With a 60 % infection rate, the risk in the placebo group is expected to be 14 %. The study numbers are based on vaccination reducing the additional risk of 8.75 % in infected children by 70 %–2.625 %, resulting in a total risk of 11.375 % in infected children and an overall risk in the treatment arm of 10.3 %. The Hazard ratio with these assumptions is: Hazard in placebo group/hazard in vaccination group = 1.38397. With an accrual time of 3.25 years, an additional follow-up of 2 years and accounting for an assumed 15 % rate of loss to follow-up, a total of 2252 children would have to be included into the study.

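### The primary log-rank test and Cox estimate leave out family history and the genetic risk score, forgoing a small, nearly free gain in precision

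*Protocol article*

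**What the plan says.** In the protocol article, section 9 (Statistics), the group difference "will be tested by the log-rank test at the two-sided significance level of 0.05". For the effect size, "The hazard ratio of the two groups and its 95 % confidence interval will be determined by the Cox model". Neither statement names a covariate or stratum. Site is the one covariate mentioned: "As a sensitivity analysis, the hazard ratio of the two groups will be assessed using the Cox regression when including site as covariate". The secondary endpoints follow the same methods. The test and the cumulative incidence estimates are also to allow for the periodic antibody visits.

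Section 6.2 (Inclusion criteria) sets two routes to the same requirement of more than 10% predicted risk by age 6. Without family history, a child needs one of three HLA genotype combinations, a further SNP genotype and a sex-specific score at the 98.75th centile. The other route reads "For children with a first-degree family history of type 1 diabetes, high genetic risk is defined as having HLA DR4 and DQ8", with no listed protective allele and a score above the 50th centile. Section 6.1 places this testing before the trial, and section 5 places randomisation from age 6 months.

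Section 9.2 (Study power and accrual target) gives the planning basis: "The trial numbers were determined for 70 % power to detect a 26 % reduction in islet autoantibodies in the treated group".

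**The concern.** The trial selects every child on family history and a genetic score because these predict islet autoantibodies, and then uses neither in its primary analysis. When baseline factors predict the outcome, including them in a time-to-event model usually raises power somewhat and removes the effect of chance imbalance between arms on those factors. The data are already held, and planned power is only 70%, so even a small free gain is worth having. The article does name a covariate, site, so this is a stated choice and not merely a detail left out of a condensed text.

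**Working it through.** **1. The plan's own figures (section 9.2).**

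Placebo risk by age 4: 0.6 × 17.5% + 0.4 × 8.75% = 14%. Vaccine-arm risk: 0.6 × 11.375% + 0.4 × 8.75% = 10.325%, printed as 10.3%.

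Hazard ratio, placebo to vaccine: ln(1 − 0.14) / ln(1 − 0.10325) = 1.38397, as stated ("Hazard in placebo group/hazard in vaccination group = 1.38397").

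Events for 70% power at two-sided 0.05:
- Schoenfeld: 4 × (1.960 + 0.524)² / (ln 1.38397)² = 234
- Freedman: (1.960 + 0.524)² × (2.38397 / 0.38397)² = 238

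Event probability: exponential hazards, uniform accrual over 3.25 years, then 2 years of follow-up. I assume the age-4 risk builds up over the 3.5 years from age 6 months. The mean probability is then 0.1251.

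Sample size with 15% loss: 234 / 0.1251 / 0.85 ≈ 2200, or 238 / 0.1251 / 0.85 ≈ 2238, against the stated 2252. With 2252 × 0.85 = 1914 evaluable children, unadjusted power is 71.1%. If the age-4 risk is spread over 4.0 years instead, that power is 65.7%, so its level depends on this assumption.

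**2. What adjustment adds.**

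Simulation: 1914 evaluable children, overall arm risks held at 14% and 10.325% at 3.5 years, about 239 events, 5000 runs per scenario. It compares an unadjusted Cox model with one adjusted for family history (FH), a standardised score, or both. The documents give no prognostic strength and no FH prevalence, so both are assumptions. The effective-size ratio is the squared ratio of mean z values.

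| Assumed effects | Power, unadjusted | Power, adjusted | Effective-size ratio |
|---|---|---|---|
| FH HR 1.5 (30% prevalence) | 70.8% | 71.1% | 1.0047 |
| FH HR 2 (30%) | 70.4% | 71.3% | 1.0195 |
| FH HR 2 (50%) | 70.2% | 70.5% | 1.0161 |
| Score HR 1.2 per SD | 71.3% | 71.4% | 1.0048 |
| Score HR 1.5 per SD | 70.2% | 71.2% | 1.0229 |
| FH HR 1.5 (30%) and score 1.2 | 71.3% | 72.0% | 1.0097 |
| FH HR 2 (30%) and score 1.5 | 70.0% | 71.7% | 1.0450 |
| FH HR 3 (30%) and score 2.0 | 69.9% | 75.4% | 1.1453 |

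The Monte Carlo standard error of each power difference is 0.2 to 0.5 points. Outside the last row, the gain equals about 0.0047 × 1914 ≈ 9 to 0.0450 × 1914 ≈ 86 evaluable children. The simulation uses exact event times, so it does not test the planned handling of periodic visits.

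**3. Are very strong effects plausible here?**

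In the last row, the 10th-percentile placebo risk is 3.7% at 3.5 years. On a constant hazard to age 6 (5.5 years), this becomes 1 − (1 − 0.037)^(5.5/3.5) ≈ 5.8%, well under the 10% entry threshold. For FH HR 2 with score 1.5, the 10th percentile is 6.8%, which becomes about 10.5%, roughly at the threshold.

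**4. Chance imbalance.**

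With 957 per arm, 30% FH and HR 2 (assumed), a 2-SD imbalance is 2 × √(0.3 × 0.7 × 2 / 957) ≈ 4.2 points. The log hazard ratio shifts by about ln(1.321 / 1.279) ≈ 0.032. The standard error at 239 events is 2 / √239 ≈ 0.129, so the shift is about 0.25 standard errors. Expected z is about 2.5 against a critical value of 1.96.

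**5. Distance to 80% power.**

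(1.960 + 0.842)² / (1.960 + 0.524)² ≈ 1.27, so 80% needs about 27% more events (298 to 303 against 234 to 238).

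**The case against.** An unadjusted log-rank test with a Cox hazard ratio is a valid primary analysis in a 1:1 randomised trial. Type I error is controlled, and the error rate already allows for chance imbalance. Stratification factors or further covariates may appear in the full protocol or SAP, which are not shown. Selection also narrows the range of both factors: each route is set to the same threshold, and children without family history come only from the top 1.25% of scores. All of this stands, and it limits the point to efficiency. It does not remove it, because the threshold is only a floor and the family-history route admits the upper half of the score distribution.

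A reader might infer something stronger: that the unadjusted analysis drops power to about 66% to 68%, and that adjustment is worth some 180 children (8% of 2252). The documents do not support this. The lower power appears only if 0.7226 (1 / 1.38397) is treated as the hazard ratio conditional on baseline risk. The protocol derives it from overall arm risks, "With a 60 % infection rate, the risk in the placebo group is expected to be 14" percent and "an overall risk in the treatment arm of 10.3" percent, so it is a marginal ratio. With those risks held fixed, unadjusted power stays near 70%. The 8% also needs a strong assumed spread of baseline risk (log-hazard SD 0.7). Nor is the unadjusted hazard ratio biased: marginal and conditional hazard ratios are different quantities, and the trial was sized on the marginal one.

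**Conclusion.** The point holds as a minor efficiency improvement. As stated, the primary test and estimate use no baseline risk factor, although two relevant ones are known for every child before randomisation. Under weak to moderate prognostic effects, adjustment gains about 0 to 2 percentage points of power, or roughly 0.5% to 4.5% in effective sample size. About 5 points would need very strong effects, which sit poorly with the entry threshold. Protection against chance imbalance is a modest further benefit. The gain is small because only about 12.5% of children are expected to have an event. The omission and the likely direction of the gain are firm; its size rests wholly on assumed prognostic strengths. Adjustment does not turn a 70% trial into an 80% one.

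**What to change.** Before unblinding, pre-specify first-degree family history and the genetic risk score in both the primary test and the primary estimate, so that the two condition on the same factors. One form is a Cox model stratified by family history, with the score as a covariate, using its score or Wald test for treatment as the primary test. Scale the score within family-history group, because the two routes have different cut-offs. Two factors are enough: section 6.1 describes scores that already draw on HLA and non-HLA variants, and HLA eligibility differs by route, so a separate HLA term would overlap with both.

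Keep the planned allowance for periodic assessment visits in the adjusted analysis. Retain the unadjusted log-rank test and Cox model as sensitivity analyses, and state that the adjusted hazard ratio is conditional on the two factors. If the full protocol or SAP already adjusts or stratifies for them, align the published description. If the sponsor prefers the unadjusted primary analysis, a sentence of justification would do.

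The cost is SAP wording, plus a protocol change if the full protocol fixes the same unadjusted analysis. No new data are needed, and about 239 events easily support two factors. The last visit is expected in October 2029.

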### Exploratory analyses

9.1

Exploratory analyses (inflammatory markers, immune cell populations, metabolomics, islet function markers, vitamin D3 concentrations, and virus exposure) may be assessed after completion and unblinding of the study and may be conducted later. Results of exploratory analyses will not be part of the clinical study report. A separate analysis plan on exploratory outcomes will be developed before these analyses are performed.

### Study power and accrual target

9.2

The sample size calculation was based on the numbers needed to test the hypothesis that COVID-19 vaccination will reduce the incidence rate of islet autoantibodies in children with a high genetic risk to develop type 1 diabetes. The trial numbers were determined for 70 % power to detect a 26 % reduction in islet autoantibodies in the treated group at a two-tailed significance of 0.05. The expected infection rate until age 2.5 years used to determine the trial numbers will be 60 %. The trial numbers were based on a 2-fold increase in the risk for islet autoantibodies in infected versus non-infected children. Therefore, the risk by age 4 years is expected to be 8.75 % in uninfected children and 17.5 % in infected children. With a 60 % infection rate, the risk in the placebo group is expected to be 14 %. The study numbers are based on vaccination reducing the additional risk of 8.75 % in infected children by 70 %–2.625 %, resulting in a total risk of 11.375 % in infected children and an overall risk in the treatment arm of 10.3 %. The Hazard ratio with these assumptions is: Hazard in placebo group/hazard in vaccination group = 1.38397. With an accrual time of 3.25 years, an additional follow-up of 2 years and accounting for an assumed 15 % rate of loss to follow-up, a total of 2252 children would have to be included into the study.

## Insurance

10

Study participants are insured with HDI-Gerling Industrie Versicherung AG.

Study participants are insured for all AEs resulting from study participation according to legal requirements (see also respective insurance policy). The insurance covers all direct or indirect damages that participants have experienced in the course of intervention with the study drug or by any study related test and examination procedures.

## Approval status

11

The study was approved by the central submission authorities Clinical Trials Information System (CTIS) for European sites and by Integrated Research Application System (IRAS) for UK sites. In UK it was approved by the local authority Medicines and Healthcare products Regulatory Agency (MHRA) and by the ethics committee East of England - Cambridge South Research Ethics Committee as well as the Health Research Authority (HRA) and Health and Care Research Wales (HCRW). In addition it is registered at Clinical Trials.gov (NCT06452654) and responsible local authorities.

## Dissemination

12

GPPAD is committed to data sharing in accordance with all applicable European and GPPAD Consortium Member State, Data Protection and Privacy Protection laws, rules and regulations.

